### Sample size calculation

According to previously randomized clinical trials, the 1-year mean change of cycloplegic SE with the DIMS spectacles, 0.01% atropine eyedrops, and the control group (single vision spectacles or placebo eyedrops) was -0.17 D, -0.38 D and -0.55 D, respectively [25]. The standard deviation (SD) of mean SE changes was around 0.5 to 0.7 in the abovementioned groups, so we choose 0.6 as the SD factor. To achieve 80% power, a significance level of 0.05, 95% CI; two-sided), and 1:1:1 allocation in a test of analysis of variance (ANOVA), the estimated sample size would be 174 participants (58 in each group) based on the calculation using the software G*Power 3.1. With the estimated dropout rate of 25% over the 1.5-year follow-up, a final sample size is 234 participants (78 in each group).

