### Statistical analysis

The database of examination parameters and questionnaire items of this study will be constructed with Microsoft Excel software (Redmond, WA, USA). Only the data from the eye with less SE (more myopic or less hyperopic) in each child will be used for identifying refractive status and ocular parameter analysis. Continuous variables will be expressed as mean (SD). Categorical variables will be expressed as frequency and percentage. The independent Student’s t-test, ANOVA, or Pearson’s chi-square test will be adopted to compare the differences between groups in terms of refractive error, demographic characteristics, and questionnaire items. Repeated measures ANOVAs will be used to test the interaction effect of time and treatment for the repeated measures during the follow-up examinations. Statistical analysis will be carried out using IBM SPSS Statistics 26 (IBM Corp., Armonk, N.Y., USA). All p values < 0.05 are considered statistically significant.

For the analysis of the primary outcome, the 1.5-year myopic shift of SE is calculated as the difference in SE between visits at baseline and at Month 18. The changes in SE over the 1.5-year follow-up period will be compared using ANOVA. The post hoc test will be carried out with Bonferroni correction to minimize the potential type I error due to multiple comparisons. The efficacy of myopic shift retardation of the therapeutic intervention is determined by dividing the difference in myopic shift between the treatment group and the control group with the myopic shift in the control group. The intention-to-treat analysis will be adopted to address the issue of loss to follow-up. The missing data in the repeated measures analysis will be dealt with generalized estimating equations (GEE). With one within-subject factor (time), one between-subject factor (treatment assignment) and their interactions, GEE will be employed to determine the treatment effect on the primary outcomes adjusted for some confounding factors, including age, gender, baseline SE, number of myopic parents, time spent on near works and outdoor activities.

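### The evaluable sample size of 174 does not follow from the stated SD of 0.6 (which gives 147), and the stated 80% power covers only the three-group F-test, not atropine versus control (about 19% at the planning values).

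*Protocol article*

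**What the plan says.** All planning inputs are in the protocol article, Sample size calculation. The 1-year mean change in cycloplegic SE for DIMS, 0.01% atropine and control "was -0.17 D, -0.38 D and -0.55 D, respectively". The SD "was around 0.5 to 0.7 in the abovementioned groups", and the text continues "so we choose 0.6 as the SD factor". The design target is given as "To achieve 80% power, a significance level of 0.05, 95% CI; two-sided", with "1:1:1 allocation in a test of analysis of variance (ANOVA" as the test. From G*Power, "the estimated sample size would be 174 participants (58 in each group"). The inflation step reads "With the estimated dropout rate of 25% over the 1.5-year follow-up, a final sample size is 234 participants (78 in each group").

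The Statistical analysis section takes the change from baseline to Month 18 as the primary outcome, compares the three groups by ANOVA, and adds: "The post hoc test will be carried out with Bonferroni correction to minimize the potential type I error due to multiple comparisons". The number of post hoc comparisons is not given. The same section expresses efficacy as the treatment-minus-control difference in myopic shift, relative to the shift in the control group. No power is given for any pair of groups.

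**The concern.** There are two separate problems in one paragraph.

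First, every input needed to rerun the G*Power calculation is printed, and rerunning it does not return the printed answer. Either the SD or the power is wrong as written, in the paragraph that justifies enrolling 234 children.

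Second, the trial asks whether each intervention slows myopic shift relative to usual care. That is answered by pairwise comparisons, whereas the power statement concerns the omnibus F-test. With these means, the omnibus test is driven by the 0.38 D gap between DIMS and control. The assumed atropine effect is less than half of that (0.17 D). A reader who carries the 80% over to atropine versus control could take a non-significant result there as evidence of no effect, in a trial meant to inform eye care policy.

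**Working it through.** **Inputs (Sample size calculation).** Means -0.17, -0.38, -0.55 D; SD 0.6; alpha 0.05; power 80%; three equal groups; one-way ANOVA.

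**Step 1: the stated N.**
- Grand mean = -1.10/3 = -0.3667. Deviations: 0.1967, -0.0133, -0.1833.
- Mean squared deviation = (0.03868 + 0.00018 + 0.03361)/3 = 0.02416; square root = 0.1554.
- Effect size f = 0.1554/0.6 = 0.259.
- Power = P(F' > critical F), where F' is noncentral F with 2 and 3n-3 degrees of freedom and noncentrality 3n·f².

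| SD | f | n per group | Total | Power |
|---|---|---|---|---|
| 0.6 | 0.259 | 48 | 144 | 79.2% |
| 0.6 | 0.259 | **49** | **147** | 80.1% |
| 0.6 | 0.259 | 58 | 174 | 86.8% |
| 0.65 | 0.239 | 57 | 171 | 79.9% |
| 0.65 | 0.239 | **58** | **174** | 80.6% |

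The stated 174 is 27 more than the inputs require. The ends of the quoted SD range do not give it either: SD 0.5 needs 105 and SD 0.7 needs 201. Nor does a higher power target at SD 0.6: 85% gives 168 and 90% gives 192. Alpha 0.025 gives 177, which is close but contradicts the stated 0.05. SD 0.65 is the only variant tried that keeps the stated alpha and power and returns 174 exactly.

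**Step 2: dropout.** 58/(1 - 0.25) = 77.3, rounded up to 78; 3 × 78 = 234. This reproduces the plan. (Starting from 49: 49/0.75 = 65.3, so 66 per group, 198 in total.)

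**Step 3: pairwise power.** Two-sample t-test, n = 58 per group, SD 0.6, alpha 0.05/3 = 0.0167. The standard error is 0.6·√(2/58) = 0.1114 and the critical t on 114 df is 2.43. The noncentrality is the difference divided by the standard error.

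| Pair | Difference | Noncentrality | Power |
|---|---|---|---|
| DIMS-control | 0.38 D | 3.41 | 83.5% |
| DIMS-atropine | 0.21 D | 1.88 | 29.7% |
| Atropine-control | 0.17 D | 1.53 | 18.8% |

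The smallest difference with 80% power is about 0.37 D. Atropine-control at 80% power would need about 261 evaluable per group.

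If the SD was in fact 0.65, the standard error is 0.65·√(2/58) = 0.1207, the noncentralities fall to 3.15, 1.74 and 1.41, and the powers to about 76%, 25% and 16%.

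**Step 4: sensitivity of atropine-control power.** Except where noted: 58 per group, SD 0.6, alpha 0.0167, difference 0.17 D.

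| Change of assumption | Power |
|---|---|
| Two comparisons (alpha 0.025) | 23% |
| No correction (alpha 0.05) | 33% |
| All 78 per group evaluable | 26% |
| SD 0.5 | 28% |
| SD 0.7 | 14% |
| Difference × 1.5 = 0.255 D, SD kept at 0.6 | 45% |
| Difference 0.255 D, SD 0.6·√1.5 = 0.73 | 29% |
| Difference 0.255 D, SD 0.6 × 1.5 = 0.9 | 19% |

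The last three rows assume that the 1-year difference grows in proportion to time up to Month 18. The documents give no 18-month figure.

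**The case against.** The strongest defence has five parts.

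- **The N error harms nothing.** This stands for the omnibus test: 174 exceeds 147, and both 0.6 and 0.65 lie within the quoted SD range. It remains a printed result that its printed inputs do not give.
- **The protocol claims 80% only for ANOVA.** This also stands. The text ties the figure to that test and nowhere promises it for atropine. The problem is that the contrasts which define efficacy have no stated power, so the only figure available is one that does not apply to them.
- **DIMS versus control is adequately powered.** True at SD 0.6 (83.5%). It would therefore be wrong to say that the 80% fails for every pair.
- **The 19% is one point in a range.** True. It depends on three comparisons, full dropout, the 1-year difference and SD 0.6. Every scenario above still lies far below 80%.
- **The adjusted GEE may be more powerful than an unadjusted t-test.** Possible, but the protocol states no gain, so none can be credited.

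Two stronger readings are tempting and are not supported. A reader might infer that a non-significant atropine result is near-certain and uninformative. At the planning values its probability is about 81%, in the most favourable 18-month scenario about 55%, and the estimate and its interval would still carry information. A reader might also infer that the Bonferroni step is a mistake. It is a valid, pre-specified choice. A closed test (F-test, then unadjusted pairs) or Holm would gain some power, but a closed test lifts atropine-control only to about 33%, gives up simultaneous intervals and, with pooled-error pairwise tests, leans on equal variances.

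**Conclusion.** The point holds in two parts. The sample size as printed is not reproducible: the stated inputs give 147, the text says 174, and at 174 and SD 0.6 the omnibus power is 86.8%. This rests on the document's own figures alone; only the explanation by SD 0.65 is inferred. The discrepancy does not leave the omnibus test underpowered.

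Separately, the 80% does not carry over to two of the three pairwise comparisons. Atropine versus control has about 19% power at the planning values, and between 14% and 45% across the alternatives for SD, number of comparisons, dropout and growth of the effect to Month 18. This is a matter of stating the design's limits correctly; it does not invalidate the design.

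**What to change.** In the Sample size calculation section:

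1. Make SD, N and power agree. If 0.65 was used, state SD 0.65 with 174 evaluable (80.6% omnibus power). If 0.6 is the intended SD, state that 174 evaluable gives 87% omnibus power.
2. Say that the means are 1-year changes while the primary test is at Month 18, and what is assumed about the difference and SD at that time.
3. State that the power refers to the omnibus F-test. Add the power for each pair at the planned Bonferroni level, with the number of comparisons, SD and evaluable N used, so that a non-significant atropine-control result is not read as coming from an 80%-powered comparison.

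The cost is a few sentences and the visibility of less favourable pairwise figures. Enrolment stays at 234. Replacing Bonferroni by a closed or Holm procedure is optional and not part of this correction.

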### Statistical analysis

The database of examination parameters and questionnaire items of this study will be constructed with Microsoft Excel software (Redmond, WA, USA). Only the data from the eye with less SE (more myopic or less hyperopic) in each child will be used for identifying refractive status and ocular parameter analysis. Continuous variables will be expressed as mean (SD). Categorical variables will be expressed as frequency and percentage. The independent Student’s t-test, ANOVA, or Pearson’s chi-square test will be adopted to compare the differences between groups in terms of refractive error, demographic characteristics, and questionnaire items. Repeated measures ANOVAs will be used to test the interaction effect of time and treatment for the repeated measures during the follow-up examinations. Statistical analysis will be carried out using IBM SPSS Statistics 26 (IBM Corp., Armonk, N.Y., USA). All p values < 0.05 are considered statistically significant.

For the analysis of the primary outcome, the 1.5-year myopic shift of SE is calculated as the difference in SE between visits at baseline and at Month 18. The changes in SE over the 1.5-year follow-up period will be compared using ANOVA. The post hoc test will be carried out with Bonferroni correction to minimize the potential type I error due to multiple comparisons. The efficacy of myopic shift retardation of the therapeutic intervention is determined by dividing the difference in myopic shift between the treatment group and the control group with the myopic shift in the control group. The intention-to-treat analysis will be adopted to address the issue of loss to follow-up. The missing data in the repeated measures analysis will be dealt with generalized estimating equations (GEE). With one within-subject factor (time), one between-subject factor (treatment assignment) and their interactions, GEE will be employed to determine the treatment effect on the primary outcomes adjusted for some confounding factors, including age, gender, baseline SE, number of myopic parents, time spent on near works and outdoor activities.

The secondary outcomes include the proportion of incident myopia, the proportion of fast myopic shift of SE, and the changes in mean axial length over the 1.5-year follow-up period. The analyses on the secondary outcomes will also be conducted with intent-to-treat principles. Using exact unconditional methods based on the Farrington-Manning score statistic, we will calculate the difference in the cumulative incidence of myopia among groups of different treatment assignment. As a binary outcome, the proportion of fast myopic shift of SE will be analyzed with Pearson’s chi-square test to compare the difference among groups. In addition, time-dependent Cox regression will be adopted to control the time-varying covariate in the analysis of the incidence of myopia and fast myopic shift of SE. Just like the analysis of myopic shift of SE, we will use ANOVA and Bonferroni correction to compare the mean change of axial length in each group. GEE will also be adapted to the treatment effect on this secondary outcome with the adjustment of the abovementioned confounding factors.

The exploratory outcomes include time to myopia onset, the changes in mean subfoveal choroidal thickness and amounts of near work/outdoor activities over the study period. In the analysis of time to myopia onset, we will assess survival analysis using a Kaplan–Meier method, with the significance based on the log-rank test. As a continuous variable, subfoveal choroidal thickness will be assessed with GEE to compare the changes among the three groups. The differences in the questionnaire items among the three groups will be estimated with ANOVA test.

The interval between the baseline visit and the last follow-up visit before school entrance is defined as “preschool stage”. The interval between the last follow-up visit before school entrance and the final visit is defined as “elementary school stage”. It is estimated that there will be nine months in both stages. The changes in SE and axial length in each stage are calculated as the difference in SE and axial length between the first and the last visits in the stage. We will use a paired t-test to compare the differences in mean change of SE and axial length between preschool and elementary school stages in each group.

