This clinical trial aims to mainly assess the effectiveness of DIMS spectacle lenses and 0.01% atropine in slowing the progression of myopic spherical equivalent SE among premyopic children before and after elementary school entrance. Because less environmental and academic pressure is presumed at preschool, premyopic children in the DIMS group of this trial will be required to wear DIMS spectacle lenses for near work at home before school entry and full-time after-school entry. This paper aims to describe the rationale, study design, and methods of this clinical trial concerning the optical (DIMS spectacle lenses) and pharmacological (0.01% atropine) approaches for premyopia around the age of elementary school entrance.

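### The two treatment-versus-control contrasts are not named as primary, and plain Bonferroni after the three-group ANOVA is valid but needlessly conservative, especially for atropine

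*Protocol article*

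**What the plan says.** The Introduction gives the aim as to "mainly assess the effectiveness of DIMS spectacle lenses and 0.01% atropine in slowing the progression" of the myopic shift. That is two questions, one per active arm.

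Under Statistical analysis, the SE change from baseline to Month 18 is compared across the three arms by ANOVA, followed by: "The post hoc test will be carried out with Bonferroni correction to minimize the potential type I error due to multiple comparisons". The pairs are not listed, their number is not given, and the text does not say that pairwise tests run only after a significant ANOVA. Treatment against control appears in the next sentence, but only as an efficacy ratio (the difference in shift divided by the control arm's shift), not as a test.

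The scheme is repeated for the secondary outcome: "we will use ANOVA and Bonferroni correction to compare the mean change of axial length in each group".

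The Sample size calculation concerns the overall test only: "To achieve 80% power" at "a significance level of 0.05, 95% CI; two-sided), and 1:1:1 allocation in a test of analysis of variance (ANOVA").

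**The concern.** Two things could be better fixed.

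- **Contrasts.** A significant three-group F-test says only that some arms differ. DIMS versus atropine, which is not one of the two stated questions, can contribute to it. The plan should say which pairs answer the aim.
- **Correction.** With exactly three groups, the only joint null hypothesis behind two or more of the pairs is that all three arms are equal, and the planned ANOVA already tests that at 5%. Under closed testing, each pair may then be tested at 0.05 after a significant ANOVA. Holm over two named contrasts is also less strict than plain Bonferroni at the same error level. Dividing alpha by three therefore gives up power.

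The arm that pays is atropine, where the planning values expect the smaller difference from control.

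**Working it through.** **Inputs (Sample size calculation).** The mean 1-year SE change for DIMS, atropine and control "was -0.17 D, -0.38 D and -0.55 D, respectively". For the SD, "so we choose 0.6 as the SD factor", from a stated range of about 0.5 to 0.7. For size, "the estimated sample size would be 174 participants (58 in each group"). Differences: atropine-control 0.17 D, DIMS-control 0.38 D, DIMS-atropine 0.21 D.

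**The plan's own figure first.** Grand mean -0.367. Squared deviations 0.0387 + 0.0002 + 0.0336 = 0.0725. f = sqrt(0.0725/3)/0.6 = 0.259. The noncentral F calculation needs 49 per group (147), not 58 (174). At 174 the overall power is 86.8%. An SD of 0.65 gives exactly 58 per group. So 174 does not follow from SD 0.6. That is a separate matter, and 58 per arm is kept below.

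**Atropine versus control, analytic.** Noncentrality = 0.17 / (0.6 × sqrt(2/58)) = 0.17/0.1114 = 1.526. Pooled t on 3 × 58 - 3 = 171 df:

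| Two-sided alpha | Critical t | Power |
|---|---|---|
| 0.05 | 1.974 | 32.9% |
| 0.025 (two control pairs) | 2.261 | about 23% |
| 0.0167 (three pairs) | 2.418 | 19.0% |

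Normal approximation as a check: Φ(1.526 - 1.960) = 33.2% and Φ(1.526 - 2.394) = 19.3%.

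**Whole procedures, by simulation** (400,000 trials per scenario, 58 per arm, SD 0.6, pooled variance):

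| Rule | Atropine-control | DIMS-control |
|---|---|---|
| Bonferroni, three pairs | 19% | 84% |
| Bonferroni, two control pairs | 23% | 87% |
| Overall F at 0.05, then pairs at 0.05 | 32% | 86% |
| Holm, two control pairs | 32% | 88% |

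Holm does well for atropine because DIMS versus control usually passes 0.025 first, which leaves atropine versus control to be tested at 0.05.

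For atropine versus control, gated against three-pair Bonferroni, the range is 44% against 28% at SD 0.5, and 25% against 14% at SD 0.7.

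**Error, equal SDs.** With all arms equal, the chance of any false claim is 5.0% gated and 4.4% with three-pair Bonferroni. With atropine equal to control and DIMS differing by 0.1, 0.2, 0.38 or 1.0 D, the false atropine claim is 3.2%, 4.4%, 5.0% and 5.0% gated, against 1.6 to 1.7% with Bonferroni. Without the gate, three unadjusted tests give about 12%.

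**Error, unequal SDs.** Assume atropine equals control, DIMS is 0.38 D better, and the SDs are 0.5 (DIMS), 0.7 and 0.7. With pooled variance, the error for atropine versus control is 7.3% gated and about 6% under Holm. With SDs 0.5, 0.6 and 0.7 it is 6.9% gated. Three-pair Bonferroni gives 2.6 to 2.8%. With pair-specific (Welch-type) variances, the gated error returns to 5.0% and Holm stays below 5%.

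**The case against.** The case for leaving the text alone is substantial, and much of it stands.

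- **Bonferroni is valid.** A reader might infer that the plan inflates type I error. It does the opposite: the rule errs on the safe side.
- **The family is not stated.** Three pairs is the natural reading of an unrestricted post hoc test, but the text does not say so. With two control pairs the atropine figure is 23%, not 19%, and DIMS versus control does slightly better than under the gated rule. An analysis plan that is not shown may list the family.
- **The contrasts of interest can be guessed.** The arms are labelled as two treatments and a control, and the efficacy ratio is against control. What is missing is a statement that these two tests answer the aim.
- **The decision rule is not ambiguous.** A reader might infer that overall p < 0.05 with atropine versus control at unadjusted p = 0.03 leaves the result open. It does not: the three-pair adjusted value is 3 × 0.03 = 0.09, so that pair is not significant. The F-test makes no claim about a particular pair.
- **Simply deleting Bonferroni would be wrong.** The post hoc label suggests a gate but none is written, and ungated tests carry about 12% error. Even gated, pooled variance can let the error reach about 7% within the protocol's own SD range. Any replacement must state the gate, or use Holm, and use pair-specific variances.
- **An F-gate can still be driven by DIMS versus atropine.** This is a reason to prefer Holm over the two named contrasts.

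**Conclusion.** This is a worthwhile, low-cost improvement and not an error of validity. The two contrasts that the aim calls for should be named, and the correction is stricter than 5% family-wise control requires. At 58 per arm, SD 0.6 and the planning means, atropine versus control has about 19% power under three-pair Bonferroni (23% under two-pair), against about 32% under Holm or closed testing. DIMS versus control changes little (84% against 86 to 88%).

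The figures rest on 1-year means used for an 18-month comparison, on 58 completers per arm, and on the three-pair reading. If all 78 per arm were evaluable, the atropine figures would be 26% and 42%.

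A reader might infer that the change rescues the atropine question. It does not: 80% power for that contrast would need about 196 evaluable children per arm at alpha 0.05. The larger limit is that only the overall test was powered.

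**What to change.** In Statistical analysis, replace the Bonferroni sentence with wording such as: The two primary contrasts are DIMS versus control and atropine versus control in SE change at Month 18. They are tested by Holm's procedure at a two-sided family-wise level of 0.05: the smaller p value against 0.025 and, if that is significant, the other against 0.05. Each test uses variances estimated from the two arms compared (Welch type). DIMS versus atropine is supportive.

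An acceptable alternative is to test each pair at two-sided 0.05, with pair-specific variances, only if the overall three-group test is significant at 0.05, and to claim no pair otherwise.

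Use the chosen rule for axial length as well.

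**Cost.** Wording only; no further children, visits or data. Unadjusted 95% intervals are not simultaneous, so Bonferroni-adjusted intervals should be reported beside them. Under the gated alternative, a pair significant at 0.0167 without a significant F-test could not be claimed, which happens in about 0.3% of simulated trials at SD 0.6.

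### Intention-to-treat and unspecified GEE are named as the remedy for 25% dropout, but the month-18 ANOVA has no value for children who have left, so arm-dependent dropout can bias the SE contrast

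*Protocol article*

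**What the plan says.** All of this is in the protocol article. Under Statistical analysis, the primary measure is the myopic shift, "calculated as the difference in SE between visits at baseline and at Month 18", and the test is given as: "The changes in SE over the 1.5-year follow-up period will be compared using ANOVA". Bonferroni-corrected pairwise comparisons follow.

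Two sentences then deal with children who leave. The first is "The intention-to-treat analysis will be adopted to address the issue of loss to follow-up". The second is "The missing data in the repeated measures analysis will be dealt with generalized estimating equations (GEE". The GEE has time, treatment and their interaction, and adjusts for covariates "including age, gender, baseline SE, number of myopic parents, time spent on near works and outdoor activities". No weighting and no working covariance are given.

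For the secondary outcomes: "The analyses on the secondary outcomes will also be conducted with intent-to-treat principles". Axial length is compared by the same ANOVA with Bonferroni correction, and GEE is used again for the adjusted effect.

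Under Sample size calculation, 58 per arm are needed for the ANOVA, and then: "With the estimated dropout rate of 25% over the 1.5-year follow-up, a final sample size is 234 participants (78 in each group".

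**The concern.** The article names two methods as the answer to loss to follow-up, and neither does what is said of it. Intention-to-treat defines the analysis set and the arm in which each child counts. It does not create an outcome for a child who was not measured. Without imputation, a change-score ANOVA drops every child who has no month-18 SE.

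GEE does use the earlier visits of children who leave. Without weights, however, it is not generally valid when dropout depends on SE observed during follow-up, unless the working covariance is correct.

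Dropout of that kind is plausible in this trial. Cycloplegic refraction is repeated every three months. The arms are visibly different (spectacles, nightly drops, or usual care without a placebo). The inclusion criteria require a parent with moderate myopia, so families know the risk. A control family that learns of a shift may leave to seek treatment. If fast-shifting children leave the control arm more often than the treated arms, the control mean at month 18 looks too good and both treatment effects are understated. Other patterns could push the contrast the other way.

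**Working it through.** **1. The plan's own figures.** 58 / (1 − 0.25) = 77.3, rounded up to 78 per arm; 3 × 78 = 234. The dropout step reproduces. In reverse, 78 × 0.75 = 58.5, so about 58 per arm would enter the month-18 ANOVA. The sample size is thus built for a test on the children who remain. (The 58 itself does not follow from the stated inputs: at SD 0.6 D the noncentral F gives 49 per arm. That is a separate matter and errs on the safe side.)

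**2. Completer bias without simulation.** With a dropout fraction of 0.25 in each arm, the completer mean minus the full-arm mean equals 0.25 × (completer mean − mean that dropouts would have had). The bias in an arm contrast is therefore 0.25 × (between-arm difference in that gap). If the gap differs by 0.3 D, the bias is 0.25 × 0.3 = 0.075 D. If the gap is equal in all arms, the bias is zero.

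**3. Simulation.**

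From the article: 1-year changes of −0.17, −0.38 and −0.55 D (DIMS, atropine, control), SD 0.6 D, six follow-up visits at months 3 to 18, and 25% dropout by month 18.

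Assumed, not in the article:
- linear shift, so the true month-18 differences are 1.5 × (0.55 − 0.38) = 0.255 D (atropine − control) and 1.5 × (0.55 − 0.17) = 0.57 D (DIMS − control);
- measurement SD 0.2 D;
- monotone dropout that follows a logistic model on the last observed change, with odds rising 1.65-fold per 0.5 D of myopic shift.

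The SD is run at two values. One is 0.6 D at month 18, taking the planning SD as it stands. The other is 0.84 D, which is what a 1-year SD of 0.6 D becomes at 18 months under linear random slopes.

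Atropine − control at month 18 (true 0.255 D):

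| Dropout depends on SE in | 18-month SD | Completers | GEE, exchangeable | Likelihood model, unstructured |
|---|---|---|---|---|
| controls only | 0.6 D | 0.21 | 0.23 | 0.26 |
| controls only | 0.84 D | 0.15 | 0.19 | 0.25 |
| all arms equally | 0.6 D | 0.26 | 0.26 | 0.26 |
| all arms equally | 0.84 D | 0.26 | 0.26 | 0.26 |

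The 0.25 in the second row is 0.251 D, within simulation error of the true value. At SD 0.6 D with controls-only dropout, completers lose about 0.05 D of 0.255 D (about 19%) and exchangeable GEE loses about 0.03 D (about 11%). GEE with an independence structure gives the completer result. If the treated arms have half the control arm's log-odds slope, completers give 0.23 D and exchangeable GEE 0.24 D at SD 0.6 D.

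**4. GEE with the right covariance.** In a separate run with stronger dependence (logistic slope 2.5 per D, 18-month SD 0.6 D, controls only), GEE with the true covariance gave 0.252 D and 0.569 D against true values of 0.255 D and 0.570 D. The exchangeable structure gave 0.187 D and 0.505 D. The weakness is therefore the unspecified covariance, not GEE as such.

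**The case against.** The strongest case on the other side has four parts.

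- **GEE is already a partial remedy.** It takes in the earlier visits of children who leave and adjusts for baseline SE, age, gender and parental myopia. This stands. Dropout that depends on those covariates is covered. A reader might infer that GEE is valid only if dropout has nothing to do with SE. The documents do not support that, and step 4 shows that a correct working covariance removes the bias even when dropout follows observed SE. Completers only describes the ANOVA, not every analysis of the primary outcome.
- **The article is condensed.** Imputation rules, the working correlation and sensitivity analyses often sit in a fuller document. This stands for those details. It does not cover the sentence naming intention-to-treat as the remedy, which is wrong as written.
- **The size rests on assumptions.** Nothing in the article says that dropout will depend on SE in controls only. Treated families may also leave, for adverse events or for shift despite treatment. This stands, and it is why the size is illustrative.
- **Type I error.** A reader might infer an inflated risk of false efficacy claims. Under the mechanism described, controls look better than they are, so spurious rejections would mostly show treatment as worse.

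**Conclusion.** The point holds in limited form. The article's statement that intention-to-treat addresses loss to follow-up is incorrect. The stated month-18 ANOVAs for SE and axial length would use about 58 of 78 children per arm. GEE, as far as it is specified, does not in general protect against dropout that follows SE seen during the trial.

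A reader might go further and conclude that the primary result will be biased. The article does not support that. Material bias in the contrast needs SE-related dropout that differs between arms; an equal mechanism leaves the contrast nearly unbiased. Under the assumed controls-only mechanism, a true atropine-control difference of 0.26 D is estimated as 0.21 D (completers) or 0.23 D (exchangeable GEE) at an 18-month SD of 0.6 D, and as 0.15 D or 0.19 D at 0.84 D. The dropout odds, measurement SD and linear shift are assumptions.

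This should be fixed. It is a planned loss of one quarter of the children, and the better analysis uses data that will be collected anyway.

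**What to change.** - Make the month-18 arm contrasts from one likelihood-based repeated-measures model the primary analysis of SE change. Use all six follow-up visits, arm by visit, baseline SE, the randomisation strata and an unstructured covariance. Use the same model for axial length. Multiple imputation before the ANOVA is an acceptable alternative.
- Delete the statement that intention-to-treat addresses loss to follow-up. Keep intention-to-treat as the definition of the analysis set, and state the missing-data assumption separately.
- Add one delta-adjusted sensitivity analysis for children who leave.

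The cost is a rewrite of a few sentences and a little more programming, with no new data and no extra children. The model relies on dropout being explained by observed data (missing at random); the sensitivity analysis probes that assumption. The change should be made before any comparison of outcomes between arms has been seen.
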